**Figure 2 F2:**
[figure not shown]
**Graphic representation of the entire surgical procedure:** 5 Goal Oriented Phases (GOP) and possibilities for delay. Repetitions, Waiting and Additional Actions.

### Outcome measurements

If the outcome is unacceptable, despite having a perfectly efficient procedure, the procedure has still failed to reach its goal. In task analysis it is therefore important to have an objective method to verify that the goal of the procedure has been met. Goal of the operation is determined by functional outcome as perceived by the patient and position of the prosthesis.

#### Functional outcome

To measure postoperative functional outcome the validated Dutch version of the Hip disability and Osteoarthritis Outcome Score (HOOS) taken pre-operative, within one week before the operation and postoperative at 6 weeks and one year follow-up [18]. Questionnaires will be collected by local surgical staff and send to the trial committee.

#### Position of the prosthesis

AP pelvis roentgenograms are taken pre-operatively, postoperatively and during follow-up visits after 6 weeks and one year follow-up as part of the standard care.

##### Cup inclination

The radiological cup inclination as described by Murray [23] defined as the angle between the longitudinal axis and the acetabular axis when this is projected on to the coronal plane. It is measured by measuring the angle between the teardrop line and the line which divides the cup inner ellipse in halve. If the teardrop line is not clearly visible, alternatively the line between the two SI joint or the lower border of the ramus inferior can be used.

Femoral shaft alignment is measured on AP pelvis roentgenogram.

##### Leg length discrepancy

pre- and postoperative leg length discrepancy is determined on a standing weight-bearing AP pelvis roentgenogram after calibration. A horizontal line is drawn through the inferior aspect of the acetabular teardrop. Two other lines parallel to the teardrop line are drawn through the centre of the lesser trochanter of each femur. Leg length discrepancy is defined as the difference between distances from the teardrop line to the lines through the lesser trochanters of each femur. All radiographs will be analyzed by two independent surgeons, blinded to the case sequence and surgeon's expertise.

#### Complications

Postoperative complications during the follow-up will be recorded by an independent nurse practitioner.

##### Assessor

Task analysis will be performed by an independent observer.

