This calls for process instead of outcome measurement. Outcome measures are most relevant for the broader perspective since they reflect the inter-play of a wide variety of factors. With a narrow perspective, on individual learning curves, process measurements become relatively more useful. Process measurements are often only considered useful if they are assumed to correlate with clinical outcome [3]. However, considering that errors within a process can have a synergistic effect it is important to focus on all errors not just those directly associated with a poor outcome [7]. Errors can be categorised by active and latent errors. Active errors have an immediate effect on outcome, while latent errors are hidden within the system, until their synergistic effects will accumulate with resulting adverse events [8,9].

Process measurement can be performed by two methods: Implicit and explicit. Implicit methods require expert judgement, without predefined criteria. Explicit methods assess quality of care against predefined criteria or algorithms, thereby providing standardised comparative and reproducible data [7]. In this study we aim to compare several surgeons and several procedures, necessitating an explicit reproducible measurement method. A previous pilot study performed at the Orthopaedic Research Centre Amsterdam by Veth and De Beer has shown an inter-observer reliability (expressed as IntraClass Correlation Coefficient) of 0.78 to 0.91 for anterolateral minimally invasive total hip arthroplasty, demonstrating it to be a reproducible tool to evaluate a perioperative process objectively.

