##### Position of the prosthesis

position of the prosthesis will be measured on AP-pelvis x-rays by two independend assessors blinded for the case number and level of experience.

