##### Complication rate

complications: peri-operative and post-operative will be recorded by independent nurse practitioners blinded for the case number.

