### Participating centres

The study will be a cooperation between the Academic Medical Centre Amsterdam, the Onze Lieve Vrouwe Gasthuis (OLVG) Amsterdam, The Isala Hospital Zwolle and McMaster University Hamilton, Canada. Surgical procedures will be performed by several surgeons at the OLVG Hospital in Amsterdam and the Isala Hospital in Zwolle. The learning of each individual surgeon will be analysed. Analysis will be performed at the Academic Medical Centre in Amsterdam by an independent assessment committee.

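### No masking to case number and no scoring order is stated for the video scorer behind the primary outcomes, so observer expectation or drift could pass for surgeon learning

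*Protocol article*

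**What the plan says.** The Primary outcome parameters section lists nett goal-oriented action time, delay, efficiency and level of difficulty. All four come from the video task analysis. Two places describe who performs it:

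- Assessor: "Task analysis will be performed by an independent observer".
- Participating centres: "Analysis will be performed at the Academic Medical Centre in Amsterdam by an independent assessment committee".

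Neither mentions masking or the order of scoring. The Privacy section conceals the patient's identity in the recordings and says nothing about surgeon or case order.

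For other assessments the article is explicit:

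- Position of the prosthesis (secondary outcomes): measured "by two independend assessors blinded for the case number and level of experience".
- Leg length discrepancy: "All radiographs will be analyzed by two independent surgeons, blinded to the case sequence and surgeon's expertise".
- Complication rate: "recorded by independent nurse practitioners blinded for the case number".

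The Data analysis section regresses efficiency and error rate on case number. The Hypothesis section expects a plateau after 10–15 cases and a fall in errors.

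**The concern.** The study's explanatory variable is the position of a case in a surgeon's series. Anything else that follows that position is confounded with learning, and the scorer is the nearest such source.

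Two mechanisms matter:

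- **Expectation.** A scorer who knows that a video shows case 2 rather than case 19, and who knows the hypothesis, may resolve doubtful calls accordingly. This needs only knowledge of the case number, whatever the scoring order. It would favour apparent learning.
- **Drift.** The scorer's own habits may change over the series. This biases the slope only if scoring order follows case order, and it can go either way. A scorer who grows more lenient inflates learning. One who becomes better at spotting repetitions hides it.

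At stake are the main question (how many cases to proficiency) and the secondary one (whether experienced surgeons learn faster). The second is also exposed if the scorer knows each surgeon's experience.

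**Working it through.** **Step 1: is there room for judgement?** The Task analysis section treats an action as a repetition when it is repeated because progress was insufficient, and as additional when it falls outside the taxonomy. Both count as delay, and efficiency is the share of time that is not delay. Scorer discretion therefore feeds directly into the primary outcomes.

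**Step 2: what is stated for each assessment?**

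| Assessment | Role | Masking stated |
|---|---|---|
| Video task analysis | Primary | None; independence only |
| Prosthesis position, radiographs | Secondary | Case number/sequence and experience |
| Complications | Secondary | Case number |
| HOOS (patient questionnaire) | Secondary | None |

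The authors treat case number as a source of assessor bias for two secondary outcomes, but state no such safeguard for the primary ones.

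**Step 3: can the effect be sized from the document?** No. The only reliability figure is a pilot which "has shown an inter-observer reliability (expressed as IntraClass Correlation Coefficient) of 0.78 to 0.91", obtained on a different hip procedure. One minus that coefficient is 0.09 to 0.22. This can include random residual error, and agreement between observers says nothing about drift within one. Even if its square root were used as a drift, the answer would depend on unstated inputs. With an assumed efficiency SD of 4 to 12 points and an assumed learning gain of 5 to 20 points:

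- lowest: 4 × √0.09 / 20 = 1.2 / 20 = 6% of the gain
- highest: 12 × √0.22 / 5 = 5.63 / 5 = 113% of the gain

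That range is too wide to be informative.

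**Step 4: how would drift act, if present?** From Sample size: 4 surgeons × 20 cases = 80 procedures, which reproduces the article's total. Assumptions: no true learning; linear drift of D (in SDs of case-level efficiency) across each surgeon's 20 videos, scored in case order; linear regression on case number with a separate intercept per surgeon; two-sided 5% test.

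- Sum of squares of case number per surgeon: 20 × (20² − 1) / 12 = 665; for four surgeons, 2,660.
- False slope: D / 19 per case. Standard error: 1 / √2,660 pooled, 1 / √665 for one surgeon.
- Ratio: D × √2,660 / 19 = 2.71 D pooled; D × √665 / 19 = 1.36 D for one surgeon.

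Simulated rejection rates (4,000 runs per setting):

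| Assumed drift D | One surgeon, case order | Four surgeons, case order | Random order (both) |
|---|---|---|---|
| 0 | 5% | 5% | about 5% |
| 0.25 SD | 6% | 11% | about 5% |
| 0.5 SD | 10% | 27% | about 5% |
| 1 SD | 26% | 76% | about 5% |

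In case order, essentially all the drift enters the slope: for four surgeons the mean false change over the series was 0.26, 0.51 and 0.99 SD. In random order it averaged about 0. A downward drift would subtract the same amounts from a true gain.

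**Step 5: what if the surgeons' series were scored one after another?** A drift D over all 80 videos would leave 19/79 = 0.24 D within each surgeon's series, and 60/79 = 0.76 D between the first and last surgeon scored. The slope would suffer less and the comparison between surgeons more.

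**The case against.** The strongest reply is that the article is silent, and silence is not a statement that the scorer is unmasked. It stands. A reader might infer from the contrast with the radiographs that the observer is unblinded, but the article's own style argues against that: the later Complications section mentions only an independent nurse practitioner, although Complication rate says these nurses are masked. A short line about independence does not rule out masking.

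Other parts of the reply also stand:

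- **Scoring order.** A reader might assume that videos are scored as they are recorded. Nothing in Data acquisition, Task analysis, Assessor or Data analysis says so. Without it the drift argument falls and only expectation remains.
- **Direction.** A reader might suppose that drift favours learning. Nothing supports a sign.
- **Reversibility.** A reader might conclude that the damage could never be undone. The recordings are unedited; if kept, they can be coded and rescored in random order.
- **Safeguards.** Actions are strictly defined, scoring agreements are set out in an additional file, the taxonomy is fixed during analysis, waiting has a 5-second minimum, and additional actions are classed regardless of cause. These narrow discretion but do not remove the judgements in Step 1.
- **Observer and committee.** One observer may score within a committee, so the two descriptions need not conflict.

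Brevity of the article does not dispose of the point. It describes masking for other assessors, has a heading for this one, and gives independence alone. An analysis plan applied after scoring cannot supply masking.

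**Conclusion.** The point holds in this form: for the assessment that yields every primary outcome, the article states independence but neither masking to case number or experience nor a scoring order, while it does state masking for radiographic and complication outcomes. Observer expectation could therefore appear as surgeon learning. If scoring runs in or near case order, drift in either direction could distort the slope or plateau.

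The size is unknown. The rejection rates illustrate the mechanism under assumed linear drifts of 0 to 1 SD and are not estimates for this study. The 76% needs both a full 1 SD of drift and pooling of surgeons; for one surgeon with drift of 0.25 to 0.5 SD the rate is about 6% to 10%. The case for acting is that protection is cheap and guards the primary outcome.

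**What to change.** In Participating centres and Assessor, state that the scorer is masked to case number and date and, where feasible, to surgeon experience, and say whether one person or several score. Then:

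- Give the video files random codes and score them in random order, interleaved across surgeons where possible.
- Start scoring a surgeon's series only after that surgeon's final case, including any extra five procedures under the stopping rule in Sample size. Otherwise an extension would form a late, recognisable batch. The extension is triggered by major complications, not by video scores, so waiting does not obstruct it.
- Record scoring order and use it in a sensitivity analysis.
- If more than one person scores, allocate videos to scorers at random.

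The cost is file relabelling and a random list, with no extra assessor. The drawbacks are a later start to scoring and delayed per-case feedback, which matters because the Background values immediate feedback. The head-camera view or sound may still reveal the surgeon, so masking to experience may be incomplete; case number and date can still be hidden.

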##### Data analysis

A regression analysis will be performed to reveal any significant increase of efficiency or decrease of the errors rate as a function of the case number.

### Patient safety

#### Interventions

The TAASTIC trial is strictly an observational study, therefore the study must not interfere with clinical decision making. Allocation of the CFP stem to a patient is not influenced by this trial. No additional interventions will be performed to facilitate this trial.

#### Privacy

Video recordings will only be made after written informed consent by the patient. The identity of the patients is concealed in all recordings.

#### Ethical approval

Since the TAASTIC trial is an observational study, a formal ethical approval was waived for this study by the OLVG Medical Ethics Committee. The OLVG Medical Ethics Committee declared to have no objections to the TAASTIC trial.

#### Operating theatre protocol

Cameras must not compromise sterility in the operating theatre. The minimum additional person to be present during surgery is restricted to only one. Local theatre protocols apply.

